### Sample size

2.13

One study^[15]^ showed that HF patients whose NT-proBNP levels decreased by more than 30% had better clinical prognosis. In this study, it was estimated that the decrease in plasma NT-proBNP in the treatment group after treatment would reach 42%. Formula n^[16]^$n={\left[\frac{\left(u_{\alpha }+u_{\beta }\right)}{\delta /\sigma }\right]}^{2}+\frac{1}{2}u_{\alpha }^{2}$ was calculated according to the sample size, where standard deviation (instead of σ) is set to 30%, α = 0.05, uα = 1.645, β = 0.1, uβ = 1.282, and δ = 42–30 = 12.

The sample size was calculated as 54 cases, considering a withdrawal rate of no more than 20%, the sample size of this study was determined to be 130 people with a ratio of the experimental and control groups of 1:1 for 65 people in each group.

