### Study design

2.1

This randomized double-blind placebo-controlled clinical trial will investigate the efficacy and safety of SGF in DHF patients. We will recruit 130 patients with DHF from LongHua Hospital affiliated with the Shanghai University of TCM. A total of 130 participants will be equally randomized into the SGF or placebo group. Patients in the SGF group will take 4 g SGF per day for 12 weeks, while patients in the placebo group will take SGF placebo for the same duration. The trial process is summarized in Figure 1.

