#### Conventional Western medicine intervention

2.8.2

All enrolled patients will be administered basic drug therapy according to the Chinese Guidelines for the Diagnosis and Treatment of Heart Failure, Chinese Society of Cardiology (2018). Angiotensin-converting enzyme inhibitors or angiotensin receptor blockers, β-receptor blockers, diuretics, digitalis drugs, and nitrate drugs will be selected for specific situations.

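### The planned difference of 12 points is the expected SGF fall minus a prognostic cut-off, so the implied 90% power applies to a one-sample test and not to the SGF-versus-placebo comparison

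*Protocol article*

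**What the plan says.** Section 2.13 (Sample size) starts from a cited finding that "HF patients whose NT-proBNP levels decreased by more than 30% had better clinical prognosis". For this trial, "it was estimated that the decrease in plasma NT-proBNP in the treatment group after treatment would reach 42" per cent. It sets δ to 42 minus 30, which is 12, and gives the other inputs as "standard deviation (instead of σ) is set to 30%, α = 0.05, uα = 1.645, β = 0.1, uβ = 1.282". The printed formula is n = [(uα + uβ)/(δ/σ)]² + uα²/2. The result is given as 54, and then, "considering a withdrawal rate of no more than 20" per cent, becomes 65 per group and 130 in all.

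The design is a parallel-group comparison: "A total of 130 participants will be equally randomized into the SGF or placebo group" (section 2.1, Study design). The primary outcome is NT-proBNP at weeks 0 and 12 (section 2.9.1). Section 2.16 (Statistical analysis) plans a t-test between groups, or a rank sum test if the data are not normal, at P < .05 with no sidedness stated. Background treatment is common to both arms: "All enrolled patients will be administered basic drug therapy according to the Chinese Guidelines" (section 2.8.2).

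**The concern.** The 30% in section 2.13 describes individual patients: those whose NT-proBNP falls by more than that amount do better. It is not described as the mean fall expected in patients on placebo plus guideline therapy. Subtracting it from the expected SGF fall measures how far the SGF mean lies beyond a fixed benchmark. The placebo arm plays no part in that quantity.

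The trial will compare SGF with placebo, and its power depends on how much NT-proBNP falls on placebo. Because every patient receives guideline drug therapy, that fall cannot be taken as known. If the stated power belongs to another test, a reader of a null result cannot tell an ineffective product from a trial that was too small to show the effect.

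**Working it through.** **Inputs from section 2.13.** Expected SGF fall 42%; value subtracted 30%; δ = 12; SD 30; uα = 1.645 (the one-sided 5% quantile); uβ = 1.282 (90% power); loss of at most 20%; 65 per group.

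**Step 1: reproduce the plan's figure.**
- [(1.645 + 1.282)/(12/30)]² = (2.927/0.4)² = 53.55
- ½ × 1.645² = 1.35
- Sum = 54.90, which is the stated 54 if truncated (55 if rounded up)
- 54 × 1.2 = 64.8, which gives 65 per group

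This is the formula for one mean, or for a paired change, against a fixed value. Other readings do not give 54. The same formula with a two-sided quantile gives 67.6. A two-sample formula gives 108 per arm one-sided or 132 per arm two-sided. So the 90% is the power of a one-sided, one-sample test of the mean SGF fall against 30%.

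**Step 2: power of the planned comparison if 30% is the placebo fall (an assumption).** For a two-sample t-test with n per arm, the standard error is 30 × √(2/n), the noncentrality is δ divided by that standard error, and there are 2n − 2 degrees of freedom.
- n = 52 (65 × 0.8, the maximum loss): SE = 5.88, noncentrality = 12/5.88 = 2.04; power 52% two-sided, 65% one-sided.
- n = 65 (no loss): SE = 5.26, noncentrality = 12/5.26 = 2.28; power 62% two-sided, 73% one-sided.

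A normal approximation gives values about one point or less higher.

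**Step 3: other placebo falls.** The article gives no placebo value, so these are assumptions shown as a range. SGF fall 42%, SD 30, 52 per arm:

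| Assumed placebo fall | Between-arm difference | Power, two-sided | Power, one-sided |
|---|---|---|---|
| 20% | 22 | 96% | 98% |
| 25% | 17 | 82% | 89% |
| 30% | 12 | 52% | 65% |
| 35% | 7 | 22% | 32% |

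**Step 4: difference detectable with 90% power, SD 30.**

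| Evaluable per arm | Two-sided | One-sided |
|---|---|---|
| 52 | about 19 points | about 17 points |
| 65 | about 17 points | about 15.5 points |

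All four exceed the 12 points in the plan.

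**The case against.** The best defence is that 30% was a tacit stand-in for the comparator. Section 2.13 does assign its result to two groups in a 1:1 ratio, and nothing in the text excludes that intention. On that reading δ = 12 is a between-arm difference and the main fault is the one-sample formula. This is a fair reading, but it does not restore the 90%: step 2 gives 52% to 73%, depending on sidedness and losses.

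Two further objections stand as limits on the point. The quantile in section 2.13 is one-sided and section 2.16 names no side, so two-sided power alone would be too harsh; both are shown. The 20% loss is an upper bound, so results for all 65 per arm are shown too.

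A reader might infer more than the article supports:
- *That the power is undefined.* It is defined, and the calculation reproduces; it belongs to a different test.
- *That the 42% and the SD of 30% have no basis, or that the investigators never assumed a placebo change.* The article condenses a fuller protocol that is not at hand, and planning data may be set out there. All that can be said is that the article gives no placebo change and that the δ it prints does not use one.
- *That the trial is certainly underpowered.* If placebo patients fall by 20% or less, and the 42% and SD of 30 hold, power exceeds 90% on either sidedness.

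**Conclusion.** Wrong as written. In section 2.13, δ is the distance between an expected SGF mean and a within-patient prognostic cut-off, and it is used in a one-sample formula. The implied 90% power does not apply to the comparison planned in section 2.16. On the reading most favourable to the text, with 30% as the placebo fall, power is 52% two-sided or 65% one-sided at 52 per arm, and 62% or 73% at 65 per arm. For assumed placebo falls of 20% to 35% at 52 per arm, it runs from 96% down to 22% two-sided and from 98% down to 32% one-sided. These figures rest on the plan's own 42% and SD of 30, an equal SD in both arms, and a t-test on the week-12 change; the placebo values are assumptions. The conclusion that the 90% belongs to another test needs none of those assumptions, because it follows from the printed formula and inputs.

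The point overlaps with any separate comment on the one-sample formula and should be read with it. Correcting the formula alone would still leave δ without a stated control-arm change.

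**What to change.** In section 2.13:
1. Define δ as the between-arm difference (SGF minus placebo) in NT-proBNP change from week 0 to week 12.
2. State the control-arm change assumed.
3. Replace the one-sample formula with a two-sample one.
4. State whether the test is one-sided or two-sided, and make section 2.16 agree.
5. Withdraw the 90% power. In its place, give the power or the detectable difference for the fixed 65 per arm, with and without the 20% loss. With SD 30, the differences for 90% power are those in step 4 of the working.

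**Cost.** Sections 2.13 and 2.16 are revised, and the investigators must commit to a control-arm value. No extra patients or measurements are needed as long as 65 per arm is kept. The downside is a less favourable stated power. If the control-arm fall they judge likely is near 30% or more, the revised text will show that the trial is unlikely to reach 90% power at its planned size.

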### Statistical analysis

2.16

The statistical analysis will be performed using SPSS 20.0. If the measurement data are normally distributed with homogeneous variance, the mean ± standard (± s) will be used for the statistical analysis and the t-test will be used for the intergroup comparisons. If the data do not follow a normal distribution, the rank sum test will be used to make statistical inferences. Enumeration data will be statistically described as frequency, constituent ratio, and rate. Comparison of indicators with dichotomous or multi-classification disorders will be performed using the *χ*^2^ test. The rank sum test will be used to compare groups of ordered classification analysis indicators. Statistical significance will be set at *P* < .05.

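### The sample size comes from a one-sample formula at one-sided 5% but is used for each arm of a two-arm comparison; for δ = 12 and SD = 30, power is 52–73%, not 90%

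*Protocol article*

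**What the plan says.** Section 2.13 (Sample size) gives the formula n = [(uα + uβ)/(δ/σ)]² + ½uα², with inputs "α = 0.05, uα = 1.645, β = 0.1, uβ = 1.282, and δ = 42–30 = 12". For the spread it says "where standard deviation (instead of σ) is set to 30" per cent. The 42 is the fall in NT-proBNP expected in the treatment group. The 30 is a threshold from a cited study, which linked a fall of more than 30% to better prognosis. No expected change on placebo is given.

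The result is then stated: "The sample size was calculated as 54 cases, considering a withdrawal rate of no more than 20" per cent. The section ends with 130 patients randomised 1:1, 65 in each group.

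Section 2.1 describes a randomised placebo-controlled trial with equal allocation. Section 2.16 (Statistical analysis) says that for normally distributed data "the t-test will be used for the intergroup comparisons", with a rank sum test otherwise, and "Statistical significance will be set at" P < .05. It does not say whether tests are one-sided or two-sided.

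**The concern.** The formula answers a different question from the one the trial asks. It sizes a single group whose mean change is tested against a fixed value, or a set of paired differences. In a comparison of two independent arms the estimated difference carries sampling error from both arms, so for the same δ and SD each arm must be about twice as large. Section 2.13 takes the single-group answer and uses it as the size of each arm.

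The significance level adds to this. A uα of 1.645 is the one-sided 5% quantile, whereas P < .05 with no further comment is usually read as two-sided.

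NT-proBNP is the primary outcome, so the stated power is the design's main claim. If a null result is read as coming from a 90%-powered trial, it will be given more weight as evidence of no effect than the design supports.

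**Working it through.** **Inputs.** From 2.13: δ = 12, SD = 30 (so δ/SD = 0.40), uα = 1.645, uβ = 1.282, withdrawal at most 20%, 65 per arm. From 2.16: intergroup t-test, P < .05, sidedness not stated, so both are shown. My assumption: 12 points is the between-arm difference, which means a 30% fall on placebo.

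**1. Reproducing the plan's figure.**
- [(1.645 + 1.282)/0.40]² = (2.927/0.40)² = 53.55
- ½ × 1.645² = 1.35
- n = 53.55 + 1.35 = 54.90, stated as 54.

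The plan's number therefore comes from the one-sample form at one-sided 5%. An exact one-sample t-test with these inputs has 89.6% power at n = 54 and 90.0% at n = 55. The 90% belongs to that test.

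**2. From 54 to 65.** The article does not show this step. 54 × 1.2 = 64.8 rounds to 65, so multiplication by 1.2 is the likely route. To have 54 left after a 20% loss needs 54/0.8 = 67.5, so 68. As planned, 65 × 0.8 = 52.

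**3. The two-sample formula.** Per arm, n = 2[(uα + uβ)/(δ/σ)]² + ¼uα².
- One-sided 5%: 2 × 53.55 + ¼ × 1.645² = 107.10 + 0.68 = 107.8, so 108. With 20% withdrawal, 108/0.8 = 135.
- Two-sided 5%: 2 × (3.242/0.40)² + ¼ × 1.96² = 131.38 + 0.96 = 132.3, so 133. With 20% withdrawal, 133/0.8 = 166.25, so 167.

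**4. Power of the planned trial.** This is the power of a two-sample t-test from the non-central t distribution, with non-centrality 12/(30 × √(2/n)) and 2n − 2 degrees of freedom.

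| Evaluable per arm | Non-centrality | Two-sided 5% | One-sided 5% |
|---|---|---|---|
| 65 (no withdrawal) | 2.28 | 61.9% | 73.3% |
| 54 (the stated size) | 2.31 × 0.90 = 2.08 | 54.0% | 66.3% |
| 52 (20% withdrawal) | 2.04 | 52.4% | 64.8% |

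**5. What the design can detect (two-sided 5%, SD 30, same method).**

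| Evaluable per arm | 80% power | 90% power |
|---|---|---|
| 65 | 14.9 points | 17.2 points |
| 52 | 16.6 points | 19.3 points |

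**6. Dependence on the placebo response.** The 42% fall on treatment and SD 30 are kept, with 52 per arm. The placebo values are assumptions, since the article gives none.

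| Assumed placebo fall | Difference | Two-sided | One-sided |
|---|---|---|---|
| 30% | 12 | 52% | 65% |
| 25% | 17 | 82% | 89% |
| 22% | 20 | 92% | 96% |
| 20% | 22 | 96% | 98% |

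**The case against.** The strongest objection is that 2.13 never calls 12 points a between-arm difference. The 30% is a prognostic threshold and no placebo response is stated. If placebo patients fell by only 20–22%, 52 per arm would give over 90% power even two-sided (step 6). This stands, and it limits the claim: a reader might infer that the trial is certainly underpowered, and the article does not support that. It supports a narrower statement. The 90% does not follow from the stated inputs for the two-arm test, and at a difference of 12 points it is not reached. The same objection shows that δ has no stated meaning for a comparison with placebo, which is itself a reason to rewrite the section.

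A reader might also infer that the trial has only an even chance of success. That describes one corner of the range: two-sided testing with the maximum withdrawal. The article allows for no more than 20% loss and leaves sidedness open in 2.16, so the fair range at 12 points is 52–73%. For the same reason the one-sided uα is an inconsistency to be reconciled, not a proven error.

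Three other defences fail.
- *The 54 might be a total.* Allowing 20% withdrawal would then give about 65–68 patients in all, not 130.
- *The SD might be smaller.* With 52 per arm, 90% power at 12 points needs an SD of about 21 one-sided or 19 two-sided, and the article states 30.
- *A later analysis plan might settle it.* It could fix the sidedness, but it cannot make a one-sample n right for two arms.

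Rounding 54.9 down to 54 and multiplying by 1.2 are minor. They cost a few patients per arm and do not drive the result.

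**Conclusion.** The point holds. Section 2.13 uses a one-sample formula at one-sided 5% for a trial that 2.16 analyses as a two-group comparison, and the article's own text is enough to show it. At δ = 12 and SD = 30, power is 62% (two-sided) or 73% (one-sided) with all 65 per arm analysed, and 52% or 65% with 52 per arm. Every one of these falls short of the 90% implied by "β = 0.1, uβ = 1.282"; the most favourable is about 17 points below it.

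The figures rest on three assumptions: that 12 points is the between-arm difference, that 30 is the SD of individual percentage changes, and that a t-test is used. The conclusion that the formula does not fit the design depends on none of them.

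**What to change.** Keep 130 patients and make these changes:

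1. In 2.13, replace the formula with the two-sample form, n per arm = 2[(uα + uβ)/(δ/σ)]² + ¼uα².
2. State the assumed change in the placebo arm and its basis, so that δ is a between-arm difference.
3. State the same two-sided 5% level in 2.13 and 2.16, replacing "α = 0.05, uα = 1.645" with the two-sided value 1.96.
4. Round up, and allow for withdrawal by dividing by 0.8.
5. Report what the design delivers at SD 30, two-sided. With 52 evaluable per arm: about 52% power for 12 points, 80% for about 16.6 and 90% for about 19.3. With all 65: about 62% for 12 points, 80% for about 14.9 and 90% for about 17.2.

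The cost is a rewrite of 2.13 and one line in 2.16, with no extra recruitment. The downside is a less favourable stated power, unless a justified placebo assumption supports a larger difference.

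### Enrolling 65 per arm does not cover the stated 20% withdrawal: it leaves 52 per arm, below the plan's own requirement of 54

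*Protocol article*

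**What the plan says.** Section 2.13 (Sample size) of the protocol article uses a formula with "α = 0.05, uα = 1.645, β = 0.1, uβ = 1.282", a difference δ of 12 percentage points, and a σ for which the "standard deviation (instead of σ) is set to 30"%. The result is given as follows: "The sample size was calculated as 54 cases". The section then moves to enrolment: "considering a withdrawal rate of no more than 20%, the sample size of this study was determined to be 130 people". Allocation is equal, so each arm is to enrol 65.

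The inflation step from 54 to 65 is not shown, and the 54 is not labelled as per arm or in total. No other section returns to the withdrawal allowance. Section 2.9.1 places the primary outcome, NT-proBNP, at weeks 0 and 12. Section 2.14 gives a trial length of 24 weeks.

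**The concern.** A withdrawal rate applies to the patients enrolled. To keep n completers when a fraction w withdraws, one must enrol n/(1 − w). Adding w × n to the requirement is not enough, because the extra patients are themselves subject to loss. The step from 54 to 65 looks like the second method.

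What is at stake is a stated property of the design. A reader takes the 20% in the sample-size section as the loss that 65 per arm can absorb while keeping the required number. If the enrolment target fails at that rate, the section contradicts its own figures. The allowance is not idle. Section 2.3 lets patients withdraw at any time, section 2.12 counts a patient with a severe adverse event as lost, and a patient lost before week 12 has no post-treatment NT-proBNP value.

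**Working it through.** **Inputs, all from section 2.13:** uα = 1.645; uβ = 1.282; δ = 12; σ = 30, so δ/σ = 0.4; stated requirement 54; withdrawal up to 20%; 65 per arm, 130 in total.

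**1. Reproduce the 54.** The plan's formula is n = [(uα + uβ)/(δ/σ)]² + ½uα².
- (1.645 + 1.282)/0.4 = 2.927/0.4 = 7.3175, and its square is 53.55.
- ½ × 1.645² = 1.35.
- n = 54.90. The plan states 54; rounding up would give 55.

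**2. Is 54 per arm or in total?** As a total, 54 inflated for 20% gives 65 (× 1.2) or 68 (÷ 0.8) patients overall. Neither is 130. Only the per-arm reading fits 65 per arm.

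**3. Reproduce the 65.**
- 54 × 1.2 = 64.8, rounded up to 65. On totals, 108 × 1.2 = 129.6, rounded up to 130. Both match the plan.
- 54/0.8 = 67.5, rounded up to 68 per arm (136 in total). Starting from 55: 55/0.8 = 68.75, rounded up to 69 per arm (138 in total). Neither matches the plan.

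That the plan multiplied by 1.2 is therefore inferred from the match. Steps 4 and 5 do not depend on it.

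**4. Completers at the stated rate.** 65 × 0.8 = 52 per arm, 104 in total. The requirement is 54 per arm, 108 in total. The shortfall is 2 per arm, 4 in total.

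**5. What 65 per arm does tolerate.**

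| Completers wanted per arm | Losses allowed | Rate |
|---|---|---|
| 54 (as stated) | 65 − 54 = 11 | 11/65 = 16.9% |
| 55 (54.9 rounded up) | 65 − 55 = 10 | 10/65 = 15.4% |

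**6. Power on the plan's own formula.** Solving the formula for power gives Φ(√(n − 1.353) × 0.4 − 1.645).
- n = 52: √50.647 = 7.117; 7.117 × 0.4 − 1.645 = 1.202; power 88.5%.
- n = 54: 89.6%.
- n = 55: 90.1%.

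**The case against.** The other side has five arguments.

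- **The 20% is a ceiling, not a forecast.** This is true, and if withdrawal stays at or below 16.9% the stated 54 is met. But a ceiling named in a sample-size section is the loss that the enrolment figure is meant to cover, and at that ceiling it does not. The gap lies between about 17% and 20%.
- **The × 1.2 step is not in the text.** This is correct, and it should be called an inference. The inconsistency stands without it, because 65 × 0.8 is below 54 however 65 was reached.
- **The timing of withdrawal is not given.** If the 20% is meant to accrue over all 24 weeks, more than 52 per arm could still have a week-12 value. This stands: 52 at week 12 assumes that all of the loss occurs before then.
- **The effect is small.** This also stands. Two completers per arm move power by about one point (89.6% to 88.5%), and no conclusion of the trial is likely to turn on that.
- **The formula itself is open to question.** It has no factor of 2 for comparing two arms, while section 2.16 plans intergroup tests. With the same δ, σ and 90% power, a two-arm calculation gives 2 × 53.55 = 107.1, or 108 per arm one-sided, and 132 per arm two-sided. That is a separate and larger matter. It does not excuse the withdrawal step, but it limits what can be claimed from 54, 55 or 88.5%.

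A reader might also infer that the study team would watch withdrawals against a 20% limit and so accept a shortfall. The protocol article does not support this. The 20% appears only as a planning figure in section 2.13, and the monitoring described in section 2.15 sets no withdrawal threshold.

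**Conclusion.** The point holds as an internal inconsistency in section 2.13. The enrolment of 65 per arm does not deliver the stated requirement of 54 at the stated 20% withdrawal; it leaves 52. The tolerable rate is 16.9% for 54 completers, about 3 percentage points below the stated figure. The lower rate of 15.4% depends on a different point, namely rounding 54.9 up to 55.

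The conclusion rests on reading 54 as per arm, which is the only reading that fits 130, and on applying the withdrawal rate to those enrolled. The power of 88.5% further assumes that the plan's formula is taken as given and that the whole 20% is lost before week 12.

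It would be tempting to call 55 the number this trial really needs, or to read 88.5% as its actual power at 20% withdrawal. Neither follows. Both figures describe the plan's formula, which does not have the form of a two-arm comparison. The practical consequence of the withdrawal step alone is small, but a stated design figure is wrong as written and is easily corrected.

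**What to change.** Keep 130 patients and correct the allowance in section 2.13, along these lines:

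> Given the formula above, 65 patients per arm allows for withdrawal of about 17% (11 of 65) if 54 completers per arm are required, or about 15% (10 of 65) if the formula result of 54.9 is rounded up to 55. Withdrawal of 20% would leave 52 per arm.

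Add that these figures are conditional on the sample-size formula. Add also that, if the base number is recalculated, the allowance is made by dividing it by (1 − withdrawal rate). On a larger base, repeating the multiplication would leave a larger shortfall.

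The cost is wording only. The stated tolerance becomes slightly less favourable, and no patients, visits or monitoring rules are added. If the sponsor prefers to keep the 20% claim, enrolment would have to rise to 68 per arm (from 54) or 69 (from 55). There is little reason to do that while the base number itself depends on the formula.
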